**Objective:**

This study aims to establish a smartphone-based real-life intervention platform that integrates momentary assessment and intervention into everyday life. The platform will explore the temporal directionality of contextual influences on alcohol use among individuals experiencing loneliness and craving.

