^ In essence, JITAIs use real-time analyses to determine momentary states (e.g. EMA of loneliness and alcohol craving and device-based read-outs, such as acceleration signals for physical activity detection), and controlled or randomized intervention-assignments (e.g. an instruction to engage in physical activity after a couple of high-craving ratings). However, experimental manipulations may be infeasible in everyday life due to practical or ethical reasons (e.g. participants may be unable to interrupt their task to follow intervention-instructions under high work-related stress).

Here, the Within-Person-Encouragement-Design (WPED)^
21
^ offers a viable solution through three key elements: (1) smartphone-based, randomly assigned encouragement to engage in an intervention as an instrumental variable (Encouragement), (2) the intervention (i.e. cognitive reappraisal, physical activity) itself (Treatment), (3) target variables (i.e. loneliness and alcohol craving) that are to be causally influenced by the Treatment (Outcome). Based on an instrumental variable estimation approach, a causal treatment effect on the outcome can be analyzed if a correlation between the encouragement and the treatment is present and given the theoretical assumption that any encouragement effects on the outcome are fully mediated by the treatment. The WPED combines three major approaches: (1) multilevel analyses of within-subject mechanisms, (2) experimental within-subject manipulation of the “treatment” variable, and (3) randomized encouragement as an instrumental variable to induce exogenous experimental variation if consistent adherence to the “treatment” is not realistic.

Both cognitive reappraisal and physical activity have been associated with reduced loneliness and alcohol craving.^22–26^ At the behavioral and neurobiological levels, both can improve cognition functions.^27,28^ However, they are very different in nature: on the one hand, cognitive reappraisal is a collection of “structured, goal-directed, and collaborative intervention strategies that focus on the exploration, evaluation, and substitution of the maladaptive thoughts, appraisals, and beliefs that maintain psychological disturbance.”^
29
^ In the context of AUD, at low engagement in reappraisal, greater startle reactivity to uncertain threat was associated with greater problem alcohol use.^
30
^

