**Figure 1. fig1-20552076241311731:**
[figure not shown]
Schematic overview of daily life causality testing in our study. Systematic experimental manipulation in phases of momentary loneliness/alcohol craving levels through the incorporation of cognitive reappraisal (Intervention 1), physical activity (Intervention 2), and working memory (control condition) via interactive smartphone triggers will allow to test for the (non)causal nature of real-life correlates (e.g. loneliness and alcohol craving) of alcohol intake.

Therefore, the overarching aim of our study is to establish a real-life intervention platform that incorporates a JITAI^
39
^ into everyday life to test the temporal direction of factors that lead to substance use. Our approach positions us uniquely to: (1) understand the temporal directionality of mechanisms of substance use in everyday life, (2) set the evidence-basis for an increasing number of (digital) mental health interventions designed for substance use through separating disease causes from consequences, (3) guide JITAIs^
19
^ for the right type/amount/time of support by adapting to individuals’ changing internal and contextual states.

We hypothesize (H1) that cognitive reappraisal and physical activity interventions will reduce momentary loneliness (H1a) and/or alcohol craving (H1b). In addition, we assume (H2) that decreases in momentary loneliness and/or alcohol craving will correspond to a decrease in real-life alcohol consumption.

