### Data analysis

We will analyze the resulting ILD using structural equation and multilevel modeling (MLM) with *R and Mplus*. The procedure including data preprocessing, analysis, and modeling is more detailed below. To preprocess EMA data, we will follow established state-of-the-art procedures detailed in methods guidelines.^
12
^ Physical activity data will be preprocessed by computing established metrics such as MAI and merged with the e-diary data (software Data Merger, *movisens* GmbH, Karlsruhe).

To assess the effectiveness of our interventions (i.e. cognitive reappraisal and physical activity) in reducing loneliness and cravings, we will employ instrumental variable estimation and build two-level structural equation models for path analyses,^
21
^ illustrated in Figure 5. On the first level (Level 1), we will estimate repeated measurements within subjects. In the path analyses, we will model (i) direct effects of the instrumental variable (encouragement for intervention) on the treatment (cognitive reappraisal and physical activity); (ii) the treatment effect on the target/outcome variables (i.e. loneliness or/and alcohol craving); and (iii) the residual (co-)variances (σ^2^_T_, σ^2^_0_, ψ_T0_) of the treatment (е_T_) and outcome (е_O_) on the within-subject level. On the second level (Level 2), we will estimate between subject differences in means, intercepts, and regression coefficients as random effects. Beyond two-level structural equation models, we will use established MLM procedures to test for within-subject changes in alcohol consumption and for pre–post differences in both mean levels of alcohol-use triggers (i.e. loneliness or/and alcohol craving).

For nonsystematic missing data,^
47
^ we will impute the missing values using the standard procedure.^
95
^ Specifically, we will employ the R package Multiple Imputation via Chained Equations to handle missing data through an iterative predictive modeling process.^
14

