## Expected results

We anticipate that our platform will demonstrate feasibility in administering both cognitive reappraisal and physical activity interventions, which are expected to reduce cravings and loneliness. In addition, it will facilitate the integration of experimental manipulation into participants’ daily routines, enabling effective testing of causal relationships. We expect that both cognitive reappraisal and physical activity interventions will decrease momentary loneliness (H1a) or/and alcohol craving (H1b). Furthermore, we posit that decreases in momentary loneliness and alcohol craving will be associated with a reduction in real-life alcohol consumption (H2).

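### The randomised encouragement is used only for loneliness and craving; the stated analysis of alcohol consumption does not carry it through to the causal question about drinking

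*Protocol article*

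**What the plan says.** The Objective in the Abstract reads: "The platform will explore the temporal directionality of contextual influences on alcohol use among individuals experiencing loneliness and craving". The Figure 1 legend is stronger: the experimental manipulation "will allow to test for the (non)causal nature of real-life correlates (e.g. loneliness and alcohol craving) of alcohol intake". H2, in the Introduction, is that "decreases in momentary loneliness and/or alcohol craving will correspond to a decrease in real-life alcohol consumption".

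Under Data analysis, the randomised part of the design is tied to a narrower question: "To assess the effectiveness of our interventions (i.e. cognitive reappraisal and physical activity) in reducing loneliness and cravings, we will employ instrumental variable estimation". In the path model the outcome path is "the treatment effect on the target/outcome variables (i.e. loneliness or/and alcohol craving". The Introduction's account of the encouragement design names the same two variables as its outcome.

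Alcohol consumption enters in a later sentence, set apart from the structural equation models: "we will use established MLM procedures to test for within-subject changes in alcohol consumption". The same sentence adds a pre-post comparison, but of mean loneliness and craving. No other quantitative analysis of alcohol is stated. An exploratory comparison with a no-intervention condition is planned in a subsample, without alcohol named as its outcome.

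**The concern.** The causal chain has two links: from intervention to loneliness or craving, and from loneliness or craving to drinking. Randomisation supports the first. The objective and the Figure 1 legend concern the second, and nothing stated carries randomisation that far.

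The Introduction sets its own conditions for a causal inference, including temporal order and control of hidden third variables. A multilevel model of within-person change in drinking does not meet the second condition. Being in a bar, having a bad day or being on a weekend evening can raise craving and drinking together. Everyone also passes through the same 7-day baseline, 21-day intervention and 7-day follow-up, so any change in drinking across these phases is mixed with self-monitoring, reporting fatigue and calendar time.

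The stake is the headline conclusion. The trial could show that the interventions lower craving, find that craving and drinking move together, and report a causal direction towards alcohol use that only the first half of the evidence supports.

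**Working it through.** **1. The plan's own figure.** From Sample size and power considerations: 180 × 0.8 = 144 participants, and 144 × 21 × 3 × 0.7 = 6350.4. The stated 6350 data points are reproduced. No numeric power or effect size is given, so none can be checked.

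**2. What each stated analysis can support.**

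| Question | Stated analysis | Randomised contrast stated? |
|---|---|---|
| Intervention to loneliness/craving (H1) | Instrumental-variable path model | Yes |
| Loneliness/craving to drinking (H2, objective, Figure 1) | Multilevel model of within-subject changes in drinking | No |

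**3. How much confounding it takes (illustration; all effect inputs assumed).** I took 144 people with 44 occasions each (63 × 0.7 ≈ 44), encouragement probability 2/3, encouragement lowering craving by 0.3 SD, and a true craving-to-drinking effect of zero. One unmeasured momentary factor has loading c on both craving and drinking. There were 1000 runs per setting, two-sided 5%.

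| c | Mean within-person slope | Association falsely significant | Randomised contrast significant |
|---|---|---|---|
| 0 | 0.000 | 5% | 5% |
| 0.1 | 0.010 | 12% | 4% |
| 0.2 | 0.039 | 87% | 5% |
| 0.3 | 0.088 | 100% | 5% |
| 0.5 | 0.245 | 100% | 5% |

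Check by hand at c = 0.2:
- Variance of craving = 1 + 0.3² × (2/3)(1/3) = 1.02.
- Slope = 0.2²/1.02 = 0.039.
- SE ≈ √(1/(144 × 43 × 1.02)) = 0.0126.
- z ≈ 3.1, so rejection is about 88%, in line with the simulated 87%.

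A loading of 0.2 means that the factor explains about 4% of the variance in each variable.

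**4. Precision of the randomised contrast on drinks.** At the design's two-to-one split, 6350.4 occasions give about 4234 encouraged and 2117 not encouraged. SE = √(1/4234 + 1/2117) = 0.0266 within-person SD, treating occasions as independent. Power at two-sided 5% (assumed):

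| Assumed total effect of encouragement on drinking | Power |
|---|---|
| 0.02 SD | 11% |
| 0.04 SD | 32% |
| 0.06 SD | 62% |
| 0.09 SD | 92% |
| 0.10 SD | 96% |

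These values are optimistic: they ignore random slopes, autocorrelation and days with fewer than three triggers.

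**The case against.** The best defence is that H2 is worded as an association, which a multilevel model can address; that the Objective says only that the platform will explore directionality; and that drinks are a secondary outcome. The article lists no predictors for the alcohol model, so encouragement, lags or a reverse path may appear in a fuller plan. The Introduction also refers to using time series to approximate Granger causality.

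Much of this stands. The mismatch is with the causal wording of the Figure 1 legend and with the aim of establishing direction, more than with H2 as worded. Missing lag details alone would be no finding in a condensed article. But the article does not merely omit detail. It specifies the instrumental-variable model down to its residual covariances, names loneliness and craving as its outcomes, and places alcohol outside it. Granger-type ordering, moreover, does not remove momentary confounding.

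Three stronger readings are tempting, and the text does not support them:
- **Drinking is tested pre-post.** The pre-post comparison attaches to mean loneliness and craving; for drinking the text says only within-subject changes.
- **There is no concurrent control.** Non-encouraged trigger occasions and the working memory task are concurrent controls within each person.
- **Randomisation is discarded.** It is used for H1, and for alcohol its use is unstated rather than excluded.

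**Conclusion.** The point holds in this limited form: the analysis stated for alcohol does not match the causal and directional aim stated for alcohol. H1 is not affected, and H2 can be tested as the association it describes.

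The size of the problem cannot be read from the documents. The simulation shows only that, with over 6000 occasions, weak unmeasured confounding is enough to produce a significant association where there is no effect. The rates depend on the assumed loadings, and with no confounding the association behaves correctly.

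The randomised contrast avoids this confounding but has limits. It estimates the effect of being encouraged on later drinking, not the effect of loneliness or craving itself. It may also be too imprecise for a null result to be informative if the true effect is near 0.02 to 0.04 SD.

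**What to change.** Add to Data analysis:

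1. An intention-to-treat multilevel count model of standard drinks reported after the trigger, for the next assessment interval and for the rest of the day. Compare encouraged with not encouraged, and each intervention with the working memory task, adjusting for drinks before the trigger.
2. Lagged, person-mean-centred models in both directions: loneliness/craving at t to drinks at t+1, and drinks at t−1 to loneliness/craving at t. Label these as associations, or as mediation under stated assumptions. One encouragement instrument cannot separate loneliness from craving, and a 6-minute task may affect drinking directly, so this path is not protected by randomisation.
3. A statement that any change in drinking across study phases is descriptive.

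If the sponsor prefers not to add these, limit the causal wording in the Objective and the Figure 1 legend to H1.

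The cost is analysis text and code. Drinks are already recorded at the momentary assessments, and non-encouraged trigger occasions are already in the design. Data collection and processing are expected to run to June 2027, so the text can be settled before analysis. The downside is the limited precision shown above, which should be stated alongside the result.

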## Expected results

We anticipate that our platform will demonstrate feasibility in administering both cognitive reappraisal and physical activity interventions, which are expected to reduce cravings and loneliness. In addition, it will facilitate the integration of experimental manipulation into participants’ daily routines, enabling effective testing of causal relationships. We expect that both cognitive reappraisal and physical activity interventions will decrease momentary loneliness (H1a) or/and alcohol craving (H1b). Furthermore, we posit that decreases in momentary loneliness and alcohol craving will be associated with a reduction in real-life alcohol consumption (H2).

## Discussion

In this study, we will integrate real-time mechanism-based interventions for alcohol use while simultaneously collecting data on behavioral patterns and physical activity through a smartphone app and a wearable sensor. This study marks a pioneering mechanistic investigation aimed at understanding the underlying mechanisms of action of interventions and behavioral processes among individuals with problematic alcohol use in Germany. By employing real-time data collection and momentary sensing techniques, the study specifically targets the mechanisms underlying loneliness and craving in the context of alcohol consumption.

JITAIs can be particularly valuable in the treatment of AUD, especially given the significant gaps in face-to-face treatment services.^96,97^ Potential applications of this JITAI include providing transitional support for individuals with AUD awaiting formal psychotherapeutic treatment and offering an alternative for those with milder AUD who may not require intensive psychotherapy.

Despite its potential, our current study has several limitations. Firstly, compared to an in-person intervention, we have less control over participants’ engagement with the intervention. To address this issue, we plan to closely monitor participant engagement and compliance throughout the study. In addition, the timing of a JITAI is crucial for triggering the intervention at the right moment.^
19
^ There is a risk that we may not assess craving or loneliness at the optimal times. Nonetheless, we must find a balance between the intensity of our sampling and the burden placed on participants.

The study will adopt multiple perspectives. First, it seeks to assess generalizability to other SUDs in future studies. Second, it aims to implement efficient digital interventions. For example, we can implement a progress indicator—a rotating display that shows the status of participants’ intervention progress in future work. Participants may accumulate points to reach modular intervention levels, displayed via sophisticated graphs such as growing trees with an increasing number of branches and leaves. Gamified progress indicators (scores and levels) can be implemented via the TherapyDesigner and TherapyBuilder (both movisens GmbH, Germany). Third, alternative causes and interventions for SUD will be explored. We can extend our approach to possible alternative causes of SUD and respective intervention strategies in the general populations. Importantly, insights into temporal directionality and digital intervention adherence gained from the current study will inform the development of the first evidence-based tailored and expedient JITAIs in SUD. Fourth, transferability and scalability to other sociocultural contexts can be explored in future studies. Ultimately, we will develop an in-silico model of losing and regaining control in alcohol use based on variational autoencoders and provide evidence-based treatment options across cultures.

## Conclusions

Our real-life intervention platform is designed as a robust tool for discerning the directionality of effects from time series data related to everyday influences on SUD. This study may pave the way for low-threshold prevention, clinical treatment, and therapy tailored to the diverse contexts of SUD, thereby facilitating rapid advancements in SUD healthcare. Moreover, our findings hold the potential to establish an insights framework for developing effective strategies to manage substance use risks in everyday life.
